### 3.2. Randomisation, Allocation, and Blinding

All study participants will receive 5% sodium carbonate and dimeticone, with one treatment per foot. Randomisation will be carried out at the treatment level and not the individual level. Trained nurses will perform the intervention. It is not possible to blind the intervener administering the treatment because 5% sodium carbonate will require soaking the foot, whereas NYDA^®^ will be applied directly to each lesion. As the two treatments will not change the skin colour of the feet, the principal investigator will be a blinded observer.

### 3.3. Recruitment Strategy

Children deemed eligible for the study will be recruited at school. A trained research assistant will briefly explain the research and after obtaining informed consent, the research assistant will visit the home with the child. The assistant will meet the caregiver of the child at home and ask if they can set up a meeting to explain the study. If the caregiver agrees, they will be given an informed-consent sheet and the research assistant will explain the subject of the investigation to the participating children and their caregivers using the explanatory documents, and will obtain their consent using the study consent form. The documents are written in the local language and English. They will be given time to ask questions for clarification before signing the informed-consent form and assent form (for children aged 13 years and older), and will be informed of their right to withdraw at any point.

There will be a health talk on tungiasis management and prevention for the community and schools before starting the study. The talk will be given through the Japan International Cooperation Agency partnership programme “Sustainable tungiasis control project in Homa Bay County, Kenya”.

According to previous studies, a longer observation period is required to have a better understanding of the outcome; thus, in this study, the primary and secondary observation periods are set to 7 days, including the suppression of new flea-proliferation, because we deduct 20 days (the period until it becomes an adult) from the 4–6 week flea lifespan [2,3,4]. Since the growth level of the target lesions is stage II or III [2], this observation period is considered sufficient. The time of intervention is set as day 1, according to the studies conducted by Ambenje et al. [14] and Nordin et al. [32]. Interventions will be administered after school in primary and secondary schools, in a place where participants feel comfortable answering questions and undergoing treatment applications. Due to the potential hazards of sodium carbonate, a well-ventilated place will be chosen.

A structured questionnaire will be used to collect the data. The questionnaire is written in English, but will be translated into the local language by research assistants. The questionnaire will take 10 to 15 min to complete.

After washing the affected area with soap and running water, both treatments will be applied, one to each foot. One affected foot will be soaked in the 5% sodium carbonate solution for 15 min. The solution will be made by dissolving 50 g of sodium carbonate in a litre of warm potable water within a deep basin. NYDA^®^ will be applied to the affected area of the other foot. In a study that examined the application method using NYDA^®^, targeted application killed embedded fleas more rapidly than when the whole foot was covered [32]. This method of application to the target area will be used in the present study. The reagent will be drawn into a 5 mL syringe to which a flexible tube is affixed. Three drops of NYDA^®^ will be applied to the targeted area. Each drop corresponds to approximately 0.05 mL of NYDA^®^, and the procedure will be repeated three times within 10 min, to ensure that a maximum amount of dimeticone has entered the abdominal cone of the parasite within a short period. This requires approximately 0.15 mL per embedded sand-flea. Clean socks will be provided to cover the foot after treatment application. If the child is wearing sandals, we will provide a pair of socks with the first and second toes separated; if the child is barefoot, we will provide a pair of sandals and socks.

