## 1. Introduction

Tungiasis is a cutaneous parasitosis caused by the female sand flea *Tunga penetrans* [1], which is distributed in tropical and subtropical regions of the world. Tungiasis is prevalent in Africa and is recognised as a neglected tropical disease by the World Health Organization (WHO) and has also been predicted to be a target for future priority measures (Sankei-photo, 2019). *Tunga penetrans* is a unique species within the realm of fleas, in that non-fertilised females penetrate the skin and remain there until they die in situ after 4–6 weeks [2,3]. It is one of a few parasites that can maintain its life cycle within sleeping quarters and is capable of completing its life cycle indoors in dwellings without a solid floor [4]. Its eggs are expelled and fall directly to the floor when an infected person sleeps, or later when the bed is made. When the floor is swept, the eggs may be transferred to crevices and holes that contain sufficient organic matter for larval development. Adults emerging from pupae adhere to and penetrate the skin when a person places their bare feet on the dwelling floor [5].

Its age-specific prevalence shows a characteristic pattern, with a maximum prevalence in the elderly population and children aged 5–14 years [6]. Children with tungiasis are reported to have disproportionately high levels of absenteeism from school and perform worse academically than unaffected pupils, because constant itching and pain make it difficult for them to concentrate on schoolwork [7].

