#### Locally Available Treatments

Most clinical trials for tungiasis have studied expensive or impractical drugs such as ivermectin, metrifonate, and dimeticone, which are difficult for residents to use on a sustainable basis. In Kenya, however, communities have been successfully treating tungiasis with a herbal-formula lotion composed of neem seed and coconut oils [12]. A recent study conducted in coastal Kenyaby Elson et al. (2019) showed that although 20% neem plus coconut oils did not kill more fleas than potassium permanganate within seven days, it resulted in better secondary outcomes. Specifically, the acute symptoms were much reduced and children had higher odds of being pain-free. Another interventional study [13] was conducted in Muranga County, using 100% coconut oil. However, due to the short observation period of that study, it was unclear whether the fleas died according to their natural lifecycle or due to the intervention. The aforementioned are common local treatments in eastern Kenya, but not in western Kenya, which is far from the ocean. In western Kenya, a local practice is to use sodium carbonate, locally referred to as Magadi or Magadi soda. This naturally available chemical is used in industries for manufacturing glass, cake glazing, as an anti-caking agent for pastries, and within chemical detergents applied for various purposes in homes. Kenyan communities use Magadi to soften green vegetables and meat during cooking. It sells on the local market at approximately KES 10 (USD 0.08) for 50 g. A study conducted in 2016 demonstrated its effectiveness in Siaya County, Kenya [14] and was published after the National Policy Guideline of recommended treatments was developed in 2014. The study of sodium carbonate did not perform practical comparisons, but concluded that it has some degree of effectiveness as a treatment. There is a need to conduct a comparative study prior to including sodium carbonate within the government-recommended treatments. 

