### 3.5. Data Collection and Storage

Data will not be collected on the names and affiliations of the participants. If they wish to discontinue the interview, observation, and treatment, their decision will be respected without any objections. Participation of school children in this study is totally voluntary. Since this is a school-based study, consent will first be obtained from each school. Informed consent will then be obtained from each participant, in accordance with the Ottawa Statement, an international guideline for cluster-randomised trials. For lesions not studied, dimeticone will be applied later, if desired. The area to be observed will be marked with an oil-based pen and photographed with a smartphone. Video recordings with a smartphone will be made only at the time of intervention, to confirm the intervention method. During the treatment, skin symptoms will be monitored until the final decision on the 7th day, using a checklist. Lesions will be examined and staged according to the Fortaleza classification [2], and counted (live/dead). The cure rate will be calculated at each stage, and significant differences at each stage will be tested. Participants will be observed and queried about adverse effects, and the severity score will be used to assess symptoms of acute tungiasis, including pain and itching. Feeling and ease of each treatment will be assessed using a questionnaire. Trained nurses will monitor the participants, and interviews will be conducted under the guidance of a medical doctor at treatment initiation and during the final decision. 

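### The 20-day deduction offered for the 7-day window does not show that enrolled fleas would outlive it, so natural deaths may count as cures and slightly dilute a true deficit

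*Protocol article*

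**What the plan says.** Section 3.3 of the protocol article states that "the primary and secondary observation periods are set to 7 days" and gives two reasons. One is a subtraction: "we deduct 20 days (the period until it becomes an adult) from the 4–6 week flea lifespan". The other is lesion stage: "Since the growth level of the target lesions is stage II or III [2], this observation period is considered sufficient". Section 3.1 (stage 4 of sampling) adds that only lesions with viable fleas are enrolled. Section 3.3 also counts the intervention as day 1.

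The Introduction describes the biology on which the subtraction depends. It says that "non-fertilised females penetrate the skin and remain there until they die in situ after 4–6 weeks", and that "Adults emerging from pupae adhere to and penetrate the skin when a person places their bare feet on the dwelling floor".

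Section 2.6 classes a flea as non-viable when 15 minutes of observation show no sign of life, whatever the cause of death. Section 2.3 has both feet treated, so no lesion is left untreated for reference, and section 2.7 says that neither agent has a placebo comparison.

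Baseline Fortaleza stage is recorded. Its stated analytic use is in section 3.5: "The cure rate will be calculated at each stage, and significant differences at each stage will be tested". Section 4.1 plans a stepwise logistic regression for the primary outcome and does not name stage as a term.

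**The concern.** The subtraction is meant to show that a flea enrolled today would still be alive at day 7 if left alone. It can do so only if the 20 days are part of the 4–6 weeks. On the Introduction's account they are not, because they precede penetration. What matters is how long the flea had been in the skin at enrolment, and the article does not give this.

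The authors treat this ambiguity as a real weakness elsewhere. Under Locally Available Treatments they say of a previous coconut-oil study that "it was unclear whether the fleas died according to their natural lifecycle or due to the intervention".

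Any natural death is a cure on both feet alike and pulls the two cure rates together. In a superiority trial that costs power. Against a fixed margin of 10 points it works in favour of the test treatment whenever that treatment is truly worse. The sources quoted in section 2.8 (70% for sodium carbonate, 78% for dimeticone) leave that possibility open.

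**Working it through.** **1. The two accounts of the lifespan**

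- Section 3.3: 28 − 20 = 8 days and 42 − 20 = 22 days. The 7-day window fits under the lower figure.
- Introduction: the 28–42 days run from penetration to death in the skin, and the adult stage is reached before penetration.
- Remaining life at enrolment is therefore 28–42 days minus in-skin age at enrolment. A flea could die naturally within 7 days if it had already been embedded for more than 28 − 7 = 21 days (28-day life) or 42 − 7 = 35 days (42-day life). The article does not say whether stage II or III fleas can be that old.

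**2. The plan's sample size, used as the base**

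Inputs from section 2.8: cure 80% in both arms, margin 0.10, power 90%, α = 0.05, design effect 1.5, loss 10%.

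- With α taken one-sided: n = (1.645 + 1.282)² × 2 × 0.80 × 0.20 / 0.10², giving 275 per arm. Then 275 × 1.5 = 413 and 413 / 0.9 = 459, against 460 stated. The figure reproduces.
- Effective number per arm after loss and clustering: 460 × 0.9 / 1.5 = 276.
- The error rates below use the one-sided 0.025 level that section 4.1 sets for the main analysis.

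**3. Effect of natural death**

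Let p be the share killed by treatment and q the share of the remaining fleas that die naturally by day 7. Observed cure is p + (1 − p)q, so the observed difference is (1 − q) times the treatment-attributable difference.

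The documents give no q, so it is an assumption. The lower end is 0. For an upper bound, suppose fleas of all in-skin ages were enrolled evenly. Day 7 is six elapsed days after day 1, so q = 6/42 = 14% to 6/28 = 21%. Enrolling only viable stage II or III fleas should put q below that.

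Take a true deficit exactly at the margin (80% v 70% killed), with SE = √[(p_C(1 − p_C) + p_T(1 − p_T)) / 276] and chance of declaring non-inferiority Φ[(difference + 0.10)/SE − 1.96]:

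| q | Observed cure, control v test | Observed difference | SE | False non-inferiority |
|---|---|---|---|---|
| 0 | 80.0% v 70.0% | −10.0 points | 0.0366 | 2.5% |
| 5% | 81.0% v 71.5% | −9.5 points | 0.0360 | 3.4% |
| 10% | 82.0% v 73.0% | −9.0 points | 0.0353 | 4.7% |

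For q = 10%: (−0.09 + 0.10)/0.0353 − 1.96 = −1.68, and Φ(−1.68) is about 4.7%.

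**The case against.** Four points on the other side carry weight.

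- **The window has a second justification.** Restriction to stage II or III, with viability required at baseline, is a genuine safeguard against fleas near the end of life. It may suffice. Stage durations are in a cited source, not in the article. This stands: one of two reasons fails, and the other is plausible but not quantified.
- **The 20 days may be mislabelled.** If they meant the greatest in-skin age of a stage II or III flea, 8–22 days would remain and 7 days would be safe. The text does not say this; it describes the 20 days as time to adulthood.
- **The hypothesis is about the cure rate.** On that scale natural death is part of the outcome and the error stays at 2.5%; the inflation applies to a claim about killing by treatment. If the data behind the margin carried similar natural mortality, part of the dilution is already in the margin. The article does not settle this.
- **Stage is balanced by design.** Section 3.1 samples lesions before treatment is randomised to foot, so stage is balanced in expectation. Matching feet on stage would be a preference, not a correction.

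A reader might infer that natural death adds a large share of the cures, for example 7/42 to 7/28 = 17–25%, with false non-inferiority of roughly 8–10% or more. The documents do not support that. Those shares assume fleas of every in-skin age and seven elapsed days, whereas the trial enrols viable stage II or III fleas and observes for six.

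**Conclusion.** The 20-day deduction is invalid on the article's own description of the flea, and section 3.3 must be reconciled with the Introduction. The article therefore does not show that enrolled fleas would outlive the window, and day-7 cure may include some natural deaths.

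Their number is unknown and may be near zero. At an assumed q of 5–10%, the distortion of a 10-point deficit is 0.5–1 point, and false non-inferiority rises from 2.5% to about 3.4–4.7%. These figures rest on equal natural death on both feet, the plan's own design effect and loss rate, and a true deficit at the margin. If the two agents kill equally, shared natural death creates no bias between them.

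Nothing here makes a day-7 endpoint wrong in itself. The defect is an unsound rationale, together with stage-wise significance tests that cannot answer a non-inferiority question, since a non-significant difference within a stage is not evidence that the deficit is under 10 points.

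**What to change.** 1. Remove the 20-day deduction from section 3.3, reconcile that section with the Introduction, and justify the window from the remaining in-skin life of stage II and III fleas, stating the figures used.
2. Keep the day-7 endpoint.
3. Keep baseline Fortaleza stage as a fixed term in the primary comparison, not one that stepwise selection can drop.
4. Replace the stage-wise significance tests in section 3.5 with the risk difference and 95% confidence interval by baseline stage, and report day 3 in the same way. Show both beside the −10 point margin as supportive estimates.
5. State in the conclusion that day-7 cure includes any natural death.

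The supportive estimates should not become conditions for the claim. If half the lesions were stage II (an assumption), the effective number would be 276 / 2 = 138 per arm, with SE = √(0.32/138) = 0.048. Power for two truly equal 80% agents would then be Φ(0.10/0.048 − 1.96), about 55%, so an equally effective treatment would fail such a check about 45% of the time. Day 3 also reflects speed of kill, for which neither the margin nor the 80% rates were set.

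The cost is a change of wording and some added estimates from data already collected (stage at baseline, viability at day 3). The downside is that the stage-specific estimates will be imprecise.

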### 2.2. Justification

In this study, we will compare two treatments for which effectivities have been evaluated and studied in Kenya. Sodium carbonate is available in the local market, whereas NYDA^®^ (a mixture of two dimeticone oils with different viscosities and spreadability) is not yet available in the Kenyan market. The advantages and disadvantages are shown in Figure 2. In terms of mechanism of action, sodium carbonate can soften the tissue and push fleas out by allowing chemicals to enter the body of the flea, due to changes in osmolarity and swelling [14], while dimeticone can penetrate the abdominal cone of fleas, killing them. According to a previous proof-of-principle study [15] the mechanism of action of dimeticone is purely physical. The substance occludes the tracheae of *T. penetrans*, resulting in parasite death.

Solutions of sodium carbonate, typically containing 1% water, are used in personal skin-care products. Application to the feet results in an exposed surface area of 1120 cm^2^ (TGD, Part I, Annex VI). Considering a film thickness of 100 µm and a percutaneous absorption of 0.1%, the amount of sodium carbonate absorbed via the skin would be 0.1 mg. Assuming an exposure time of 20 min, this would amount to 0.0014 mg per application. The estimated systemic dose of sodium carbonate would be equal to 0.0014/60 = 2.3 × 10^−5^ mg/kg body weight [19]. Therefore, the exposure to sodium carbonate via the method of soaking a foot in a 0.5% sodium carbonate solution for 15 min, which is planned for this study, can be regarded as negligible.

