### 4.5. Hazards and Risks Associated with the Study

If improperly handled, or in the event of accidental exposure, sodium carbonate can pose some hazards to health and safety. If participants experience adverse effects such as irritation, blisters, or burning sensation (which generally happens when a concentrated substance gets into the eyes or is inhaled), we will immediately flush the skin with plenty of water and provide necessary treatments or refer the participant free of charge to the nearest health facility.

Another possible risk is that the child may be teased for having jiggers, since this will be revealed to other children in the school by participation in the study. Before selecting participants, we will provide information on tungiasis through health promotion, so that all children will have proper understanding, to reduce prejudice, discrimination, or stigmatisation toward people affected with the disease. By so doing, we aim to minimise the mental burden on participants. In addition, confidentiality will be maintained throughout the study. Any severe adverse reactions (such as dermatitis, fever, and headache) and events occurring during the follow-up period will be recorded and considered for potential association with the treatment.

In the case that treatment is needed at a doctor’s discretion, participants will be immediately referred to the hospital for treatment, and if the treatments show no effect they will be stopped immediately, before study completion. The treatment will be applied not only to the lesions to be studied but also to other identified lesions. In addition, excluded participants (such as people with embedded sand-fleas on only one foot) will be treated with the agent that works best when the intervention is completed.

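### Treatment delivery is stated inconsistently in three places (NYDA volume, carbonate strength, handling of non-study lesions); two of these could pull the arms together, by an amount the protocol does not allow one to derive

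*Protocol article*

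**What the plan says.** **NYDA volume.** Section 3.3 describes the control treatment as three drops, each of about 0.05 mL, placed on the lesion. It adds that "the procedure will be repeated three times within 10 min". The total need is then given in a separate sentence: "This requires approximately 0.15 mL per embedded sand-flea".

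**Carbonate strength.** Section 2.2 concludes that skin exposure is negligible for "soaking a foot in a 0.5% sodium carbonate solution for 15 min, which is planned for this study". Section 3.3 prepares the bath by "dissolving 50 g of sodium carbonate in a litre of warm potable water". The hypothesis and the sections on objectives, design, outcomes, sample size, allocation and procedure all say 5%.

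**Non-study lesions.** Section 3.5: "For lesions not studied, dimeticone will be applied later, if desired". Section 4.5: "The treatment will be applied not only to the lesions to be studied but also to other identified lesions". Neither section names the foot, and section 3.5 does not say whether the dimeticone waits until after the day 7 assessment.

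**The concern.** Each child serves as its own comparison, with one treatment per foot, and the claim sought is non-inferiority within 10 percentage points. In such a design, anything that weakens the control or carries the control agent to the test foot shrinks the observed difference and makes the claim easier to reach.

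- The NYDA item concerns delivery of the active control. Section 4.1 adopts a per-protocol approach, and section 3.5 provides for filming the intervention to confirm the method. If the volume can be read two ways, neither adherence nor the film has a fixed standard to be judged against.
- The non-study-lesion item concerns separation of the arms. The Introduction describes NYDA as spreading readily. Section 4.4 plans to analyse skin symptoms by treatment, and these are scored at the level of the foot.
- The carbonate item is of a different kind. It leaves the safety justification describing a bath other than the one in the procedure.

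**Working it through.** **1. NYDA volume (inputs from section 3.3).** Volume = drops × mL per drop × rounds.

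| Reading | Arithmetic | mL per flea |
|---|---|---|
| One round of three drops | 3 × 0.05 | 0.15 (the stated figure) |
| Three drops, three rounds | 3 × 0.05 × 3 | 0.45 |
| Three drops, then three further rounds | 3 × 0.05 × 4 | 0.60 |
| One drop in each of three rounds | 1 × 0.05 × 3 | 0.15 |

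The stated figure is reproduced only if the repeat is ignored or if the three drops are spread over three rounds, which the text does not say. The literal reading is 3 to 4 times the stated volume.

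**2. Carbonate strength and exposure (inputs from sections 2.2 and 3.3).** The recipe is 50 g / 1000 mL = 5% w/v, which is 5 / 0.5 = 10 times the strength named in section 2.2.

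The printed exposure estimate can be reproduced. A strength of 1% and a 24-hour basis (20/1440) are inferred, because they return the printed values:

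- Film volume: 1120 cm² × 0.01 cm = 11.2 mL. At 1% this holds 112 mg.
- Absorbed at 0.1%: 0.112 mg, printed as 0.1 mg.
- For 20 min: 0.1 × 20/1440 = 0.0014 mg.
- Per kg: 0.0014 / 60 = 2.3 × 10^-5 mg/kg.

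Scaling the same chain:

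- 5% for 15 min at 60 kg: 5 × 15/20 = 3.75 times, or about 8.6 × 10^-5 mg/kg.
- The same at an assumed 25 kg (the article gives no weights for children aged 8 to 14): 3.75 × 60/25 = 9 times, or about 2.1 × 10^-4 mg/kg.
- Section 3.3 soaks one foot, whereas the area in section 2.2 is for the feet. Halving the area gives 4.5 times at 25 kg, before any allowance for a child's smaller foot.

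The dose stays small in every case.

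**3. Non-study lesions.** Children with up to 20 fleas are eligible (section 2.5.2), and one to five lesions per foot are studied (section 3.1, stage 4). A child with 20 fleas therefore has at least 20 − 2 × 5 = 10 non-study lesions. On the carbonate foot, the soak reaches all of them. Section 3.5, read literally, then permits dimeticone on the same foot during follow-up. On the NYDA foot, the drops are targeted, so other lesions are treated at the outset only if section 4.5 governs. The two sections lead to different exposures on both feet.

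**4. Direction of bias, with assumed effects.** Effective lesions per arm: 460 × 0.9 / 1.5 = 276, from section 2.8. One-sided α is 0.025, from section 4.1. True rates with full delivery are set at the margin: 80% control, 70% carbonate. The chance of declaring non-inferiority is Φ[(pT − pC + 0.10)/SE − 1.96], with SE = √{[pT(1 − pT) + pC(1 − pC)]/276}.

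| Assumed departure | Chance of declaring non-inferiority |
|---|---|
| None | 2.5% |
| Control rate lower by 2 / 5 / 10 points | 7.8% / 26% / 73% |
| 10% / 20% / 30% of carbonate study lesions respond as if given dimeticone | 4.6% / 8.0% / 13% |

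A weaker bath works the other way. With both true rates at 80%, power is 84%; it falls to 64% or 29% if the carbonate rate drops by 2 or 5 points. These figures show direction only. The article gives no dose-response and no contamination rate.

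**The case against.** The strongest reply is that these are three wording faults, none of which demonstrably changes the comparison.

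- **NYDA.** One drop in each of three rounds matches every printed number. If 0.15 mL is what is intended, the risk of misreading is too much control agent, which does not favour non-inferiority. This stands in part: the text is ambiguous rather than provably wrong, but it does not say one drop per round.
- **Carbonate.** The 0.5% appears once, in a background section, against 5% throughout and an explicit recipe. It may be a slip, and a nurse following section 3.3 would not be misled. This largely stands. The item concerns the test arm and the safety text, and it gives no push towards non-inferiority.
- **Non-study lesions.** The word for later in section 3.5 may mean after day 7. Study lesions must be unclustered and clearly distinguishable (sections 2.5.1 and 3.1), and NYDA is placed lesion by lesion, so spread to study lesions is less likely. This reduces the concern without removing it, since section 3.5 sets no limit and section 4.5 says something else.

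A reader might infer that the control will be under-delivered, or that dimeticone will reach a given share of carbonate lesions and carry a truly inferior treatment inside the margin. The document supports neither. Any such share would be chosen by the reader, not observed.

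A reader might also want exposed carbonate lesions counted as not cured. That rule would penalise one arm only, and it presupposes an all-randomised analysis that section 4.1 does not define.

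**Conclusion.** The inconsistencies are real and stand in the current text. The stated NYDA volume is one third to one quarter of the literal one. The strength behind the exposure judgement is one tenth of that in the recipe. The handling of non-study lesions is described in two incompatible ways, one of which permits the control agent on the test foot during follow-up.

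The first and third items matter for inference. If the control is under-delivered, or if dimeticone is used on the carbonate foot before day 7, the bias runs towards non-inferiority and may also reach the foot-level symptom scores. How large it would be cannot be derived from the document. Both items should be settled before the first child is treated, because volumes and cross-foot use that go unrecorded cannot be recovered later.

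The second item is a correction to the safety justification and carries less weight. The recomputed dose is 3.75 times the printed one at 60 kg and about 9 times at an assumed 25 kg, before any reduction for a single, smaller foot.

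**What to change.** 1. Reconcile the passages so that each item is stated once: volume per flea together with drops per round and number of rounds (section 3.3); solution strength (sections 2.2 and 3.3); and handling of non-study lesions, including foot and timing relative to day 7 (sections 3.5 and 4.5). Which volume, strength or rule applies is for the sponsor and investigators to decide.
2. Recompute the exposure estimate in section 2.2 for the strength, soak time, treated area and body weights that apply in this trial.
3. On the case record form, record the date and foot of any dimeticone put on a carbonate foot before day 7. Treat it as a protocol deviation for the per-protocol set of section 4.1, and show the primary result with and without the lesions concerned.

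The cost is a short clarification of the protocol, one recalculated figure, one line on the record form and one extra presentation of the primary result. The sample size does not change.
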